***Eligibility Criteria***

Inclusion Criteria (to be checked during huddle/ after check-in and x-ray/ at consent):

1. All new patients with a presumptive diagnosis of knee OA
2. Aged between 45 and 89
3. K-L grade of 3 or 4 (moderate to severe)
4. KOOS JR scores 0-85
5. Able to provide informed consent

Exclusion Criteria (to be checked during huddle/ after x-ray and check-in/ at consent):

1. Prior total knee replacement
2. Prior consultation with an orthopaedic surgeon for TKR
3. Prior experience with Joint Insights
4. Patients undergoing consideration for revision joint replacement
5. Patients seeking care for a trauma condition, or psoriatic/rheumatoid arthritis
6. Non-English or Non-Spanish speakers
7. Patients with BMI below 20 or above 46

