***Outcomes***

This study will assess the impact of a technology-enabled decision aid on:

| **Outcome** | **Measure** |
| --- | --- |
| Decision quality | Knee Decision Quality Index Q3.1-3.5 |
| Concordance | Knee DQI Q1.6 & whether patient had TKA within 9 months (Athena) |
| Shared decision making | CollaboRATE survey |
| Patient/provider satisfaction with discussion | Satisfaction question |
| Consultation time | Duration of surgeon/patient consultation in minutes as measured by research assistant |
| Overall health | PROMIS Global 10 |
| Change in limitations | KOOS JR |
| Treatment selected | Treatment choice/arthroplasty rate |
| Decisional conflict | Decisional Conflict Scale 10 (low literacy) |
| Decision regret | Decision Regret Scale |

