***Sample Size***

The aim is to enroll a total of 200 subjects with randomization to either the intervention arm or the control arm of the study (100 controls and 100 interventions). The study is powered to account for 10% loss to follow-up, with a target sample size of 180 patients. We calculated the sample size for the RCT by treating the Decision Process score of the DQI as continuous. We aimed to detect a treatment effect size (i.e., Cohen’s D) as small as 0.5 (consistent with preliminary data from the first 26 subjects we have studied) with a type I error rate of 0.05 and power of 0.90, assuming equal sample size in intervention and control groups. Given our 8 randomization strata, we estimate a needed sample size of 180 participants, or 90 for each group. With an estimated loss-to-follow-up rate of 10%. Our target enrollment for the RCT is 200 participants, or 100 for each arm.

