**Data Management & Analysis**

Data collection at baseline and follow-up will be conducted as above in “Methods” section.

Data management will be conducted using REDCap as detailed above. This is a confidential and secure database protected on UT servers.

Formal comparative analysis will follow the intent-to-treat principle. Primary analysis will compare the intervention and control groups by using multiple linear regression analysis. The model will include DQI score as the response variable and, as explanatory variables, a binary indicator for the intervention group and 7 binary indicator variables representing the 8 strata in order to reflect the stratified randomization design. Additionally, as a secondary analysis, we will compare treatment decisions between the intervention and control groups by using multiple logistic regression. The model will include the treatment decision as the binary response variable and the same explanatory variables as in the linear regression model. Depending on the uptake of the intervention, additional analyses will follow the “per-protocol” principle wherein the main treatment variable will be whether the Joint Insights tool was used.

For analysis of the 3- and 6-9 month data, we will fit linear mixed models for continuous outcomes35 and generalized estimating equations logistic regression models for binary outcomes36, including indicator variables for time point, for treatment group, and for the interaction between the two (yielding treatment effects at 3 months and at 6-9 months). Owing to the balanced design, it will be possible to fit an unstructured correlation model to eliminate any sensitivity to correlation model misspecification.

Data monitoring is not required for this study. No interim analysis is planned.

This is a minimal-risk study. Although we don’t anticipate any adverse events, any adverse events will be reported to the local IRB.

The datasets used and/or analyzed during the current study are available from the corresponding author on reasonable request.

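### The 3- and 6-9-month models name neither the baseline score nor the randomisation strata, so the secondary functional results are likely to be less precise than the collected data allow

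*Protocol*

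**What the plan says.** The Protocol's Data Management & Analysis section describes three sets of models.

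- The primary model regresses the DQI score on an arm indicator and "7 binary indicator variables representing the 8 strata in order to reflect the stratified randomization design".
- The treatment-decision model is a logistic regression that takes over the same explanatory variables.
- The 3- and 6-9-month data are analysed with linear mixed models (continuous outcomes) and GEE logistic models (binary outcomes), "including indicator variables for time point, for treatment group, and for the interaction between the two". The section adds that this yields an effect at each of the two visits and that the correlation will be unstructured. It names no stratum term and no baseline value.

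Baseline scores are available. Eligibility Criteria requires "KOOS JR scores 0-85". Baseline Documentation has KOOS JR and PROMIS-10 entered in REDCap from the clinic record, without distinguishing the arms. The script for the full-tool arm says that the survey questions were answered at check-in. Both instruments are repeated at follow-up together with the Decision Regret Scale. The Outcomes table labels the KOOS JR outcome "Change in limitations", but the analysis section does not say whether the response is a change or a follow-up score.

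**The concern.** The reason given for stratum terms in the primary model is that randomisation was stratified. That holds equally at 3 and 6-9 months, yet the terms are not carried over. A baseline measurement of the same instrument is usually a strong predictor of its later value, it costs nothing here, and the named terms do not use it. One outcome is called a change while the model does not say how baseline enters.

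At stake is the precision of the functional results, which are among the stated objectives. A chance difference between arms at baseline also carries over into an unadjusted estimate. With 90 per arm the baseline difference has a standard error of 0.149 SD, so a gap above 0.29 SD arises in about 5% of trials. At a correlation of 0.5, a gap of that size moves the unadjusted follow-up difference by about 0.5 × 0.29 = 0.15 SD, a full standard error.

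**Working it through.** **Inputs from the Protocol (Sample Size).** "type I error rate of 0.05 and power of 0.90"; "treatment effect size (i.e., Cohen’s D) as small as 0.5", set for the DQI Decision Process score; "we estimate a needed sample size of 180 participants, or 90 for each group". Sidedness is not stated; two-sided is assumed.

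**The plan's own figure.** n per arm = 2(1.960 + 1.282)²/0.5² = 84.1, so 85 (86 with the t distribution, with or without 7 degrees of freedom for strata). The plan's 90 is slightly conservative: power is Φ(0.5/√(2/90) − 1.96) = 0.918. Allowing for 10% loss, 180/0.90 = 200, as stated. These figures concern the primary score only. Below, 90 per arm is borrowed as the number with data at a follow-up visit.

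**Baseline adjustment.** With arm, time and their interaction and complete data, the arm difference at a visit has SE = √(2/90) = 0.149 SD. Adding baseline as a covariate multiplies this by √(1 − ρ²), where ρ is the baseline-to-follow-up correlation. Analysing a plain change score instead multiplies it by √(2(1 − ρ)), if the SD is the same at both times. Power for a 0.4 SD difference is Φ(0.4/SE − 1.96). The Protocol does not give ρ, so a range is shown; 0.4 SD is an illustration, not a Protocol target.

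| ρ (assumed) | Variance removed | SE ratio, covariate | SE ratio, change score | 95% CI half-width, covariate (SD) | Power for 0.4 SD, covariate | Equivalent unadjusted n per arm |
|---|---|---|---|---|---|---|
| baseline not used | – | 1 | – | 0.292 | 0.765 | 90 |
| 0.3 | 9% | 0.954 | 1.183 | 0.279 | 0.803 | 99 |
| 0.4 | 16% | 0.917 | 1.095 | 0.268 | 0.833 | 107 |
| 0.5 | 25% | 0.866 | 1.000 | 0.253 | 0.873 | 120 |
| 0.6 | 36% | 0.800 | 0.894 | 0.234 | 0.918 | 141 |

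With the t distribution the power figures are 0.761 unadjusted and 0.799 to 0.916 adjusted. The covariate is at least as precise as either alternative at every correlation. A change score beats the raw follow-up score only when ρ exceeds 0.5.

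**Strata.** Let R² be the share of outcome variance that the strata explain (assumed; not in the Protocol). Stratified blocks already balance the strata, so the true SE is about √(1 − R²) times the SE that a model without strata reports. The actual type I error is then about 2(1 − Φ(1.96/√(1 − R²))).

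| R² (assumed) | True SE / reported SE | Type I error |
|---|---|---|
| 0.02 | 0.990 | 0.048 |
| 0.05 | 0.975 | 0.044 |
| 0.10 | 0.949 | 0.039 |

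A simulation (90 per arm, 8 strata balanced by arm, 4,000 runs per setting, one visit) agrees. At R² = 0.05 and ρ = 0.5 the empirical SE was 0.1465 with and without stratum terms. At R² = 0.10 the model without strata reported 0.149 where the model with strata reported 0.141, and its type I error was 0.038 to 0.041. The strata therefore alter the reported SE, not the real scatter of the estimate.

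**The case against.** The best reply is that the sentence says which terms the models include, not that they contain nothing else. The three terms define the effects at the two visits, and a separate SAP may list covariates. A reader might infer that the Protocol excludes baseline and strata; the text does not go that far. What remains is that the same section spells out stratum terms for two models, goes as far as fixing the correlation structure for the third, and leaves the strata out there. That is a stated specification to correct, not mere missing detail.

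A second reply is that baseline could be one of the repeated responses, in which case the unstructured correlation would already use it. The label "Change in limitations" points that way. But the models are for the 3- and 6-9-month data, and the interaction is said to give effects at those two times only. The reading cannot be excluded, but it fits poorly, and the two sections need reconciling in any case.

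Third, the gain is uncertain. At ρ = 0.3 it is modest (half-width 0.292 to 0.279 SD). The strata were chosen as predictors of decision quality or treatment choice, not of function, so a large R² is not supported. Both points stand and are why ranges are shown.

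Fourth, stratum terms are not free in a logistic GEE: the odds ratio becomes conditional on stratum, and sparse strata may make the fit unstable. That also stands. The follow-up questionnaires are not described as binary, so which outcome the GEE serves is unclear.

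Nor do the documents support reading this as bias. Randomisation protects the comparison, chance imbalance is already reflected in the unadjusted standard error, and nothing shows that baseline is the best predictor of dropout. The mixed model already uses the 3-month score for those missing later.

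**Conclusion.** The point holds as a matter of efficiency in secondary outcomes, and of consistency within the analysis section. The larger part is baseline: for KOOS JR and PROMIS, 9% to 36% of the variance is avoidable if ρ lies between 0.3 and 0.6, which at 90 per arm is worth 9 to 51 extra participants per arm. The smaller part is the strata: reported standard errors about 1% to 5% too wide for R² of 0.02 to 0.10, with a test that errs on the conservative side. It would be tempting to say that dropping the strata makes the functional estimates imprecise or biased; in the linear models it does neither to any material extent. All sizes rest on an assumed ρ, an assumed R² and 90 participants per arm with follow-up data. The primary DQI analysis and its sample size are untouched.

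**What to change.** In Data Management & Analysis, extend the description of the follow-up models:

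- Linear mixed models for KOOS JR and PROMIS: add the 7 stratum indicators, the baseline value of the same instrument and its interaction with time point, and state that the response is the follow-up score. With baseline in the model in this form, the arm effects are the same whether the response is the score or its change, so this also settles the label in the Outcomes table.
- Linear mixed model for decision regret: add the 7 stratum indicators only, since no baseline value exists.
- GEE models: add the 7 stratum indicators for any binary follow-up outcome, as the treatment-decision model already does. State which outcome this is and that the odds ratio is conditional on stratum.

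The cost is a few sentences and a few degrees of freedom, with no new data. The drawback is confined to the GEE models: a change from a marginal to a stratum-conditional odds ratio, and possible instability where strata are sparse. Because the trial is open label, the covariates should be fixed before outcomes are compared by arm.

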**Dissemination**

Planned publications:

1. Protocol paper
2. Results paper

Plan to follow ICMJE guidelines to determine authorship eligibility.

**Disclosures**

[name] has received personal fees from Johnson & Johnson Medical Devices and the Purchaser Business Group on Health. [name] has received personal fees from the CMS and Purchaser Business Group on Health; has stock options from Carrum Health; and has a leadership role with AAOS. [name] has royalty agreements with Wolters Kluwer and Slack Incorporated. [name] and [name] are co-developers of the Joint Insights tool; they have no personal financial interest in the tool. The University of Texas at Austin has a royalty agreement with OM1, Inc. [name] receives royalties from Wolters Kluwer.

